## Abstract

**Background:**

Joint replacement is an effective intervention for people with advanced arthritis, although there is an important minority of patients who do not improve post-operatively. There is a need for robust evidence on outcomes after surgery, but there are a number of measures that assess function after joint replacement, many of which lack any clear theoretical basis. The World Health Organisation has introduced the International Classification of Functioning, Disability and Health (ICF), which divides function into three separate domains: Impairment, activity limitations and participation restrictions. The aim of this study is to compare the properties and responsiveness of a selection of commonly used outcome tools that assess function, examine how well they relate to the ICF concepts, and to explore the changes in the measures over time.

**Methods/design:**

Two hundred and sixty three patients listed for lower limb joint replacement at an elective orthopaedic centre have been recruited into this study. Participants attend the hospital for a research appointment prior to surgery and then at 3-months and 1-year after surgery. At each assessment time, function is assessed using a range of measures. Self-report function is assessed using the WOMAC, Aberdeen Impairment, Activity Limitation and Participation Restriction Measure, SF-12 and Measure Yourself Medical Outcome Profile 2. Clinician-administered measures of function include the American Knee Society Score for knee patients and the Harris Hip Score for hip patients. Performance tests include the timed 20-metre walk, timed get up and go, sit-to-stand-to-sit, step tests and single stance balance test. During the performance tests, participants wear an inertial sensor and data from motion analysis are collected. Statistical analysis will include exploring the relationship between measures describing the same ICF concepts, assessing responsiveness, and studying changes in measures over time.

**Discussion:**

There are a range of tools that can be used to assess function before and after joint replacement, with little information about how these various measures compare in their properties and responsiveness. This study aims to provide this data on a selection of commonly used assessments of function, and explore how they relate to the ICF domains.

## Background

Lower limb total joint replacement (TJR) is one of the most commonly performed elective surgical procedures in the UK. In 2010, 76,759 hip replacements and 81,979 knee replacements were performed in the NHS [1], and it is predicted that due to increases in obesity and an aging community, these figures will rise considerably in the coming years [2]. TJR is an effective and cost-effective intervention for people with advanced arthritis [3,4], although recent evidence suggests that an important minority do not improve post-operatively [5]. This concern, along with the known variations in the provision of and outcomes from TJR [6,7] mean that there is an urgent need for robust evidence on outcomes after surgery to aid appropriate patient selection and to provide patients with realistic predictions of the likely results.

The outcome after a TJR can be assessed in a variety of different ways. In the early years of TJR common adverse events, such as infection, as well as prosthesis survival were the main issues of concern [8]. However, as prosthesis design and the control of adverse events improved, these issues become less important, and attention turned towards clinician administered tools, such as the Harris Hip Score [9] and American Knee Society Score [10], and more recently towards patient reported outcome measures (PROMs) [11]. But it is not clear what PROM domains should be assessed, or how we can best measure them.

TJR is generally undertaken to reduce pain and improve function for people with advanced osteoarthritis (OA) [12]. Pain and disability are inextricably linked in OA, as the pain is largely activity-related [13]. Although pain is often considered the most important aspect of outcome to assess, it is a purely subjective issue, and therefore difficult to ‘measure’. Function, on the other hand, is a more objective domain, and as it is closely related to pain, it would seem reasonable to concentrate our measurement efforts on function. However, there are many different ways of assessing function and a large number of variables which can influence it [14]. Furthermore, most of the standard ways used to assess function lack any clear theoretical basis [15], and there has been relatively little research on the relationships between the different approaches used.

The World Health Organisation has introduced the International Classification of Functioning, Disability and Health (ICF) [16] which provides a theoretical framework on which to base the assessment of function. As shown in Figure 1, this framework splits function into three separate domains: impairment (I), activities limitations (A) and participation restrictions (P). The value of this in the context of TJR can be illustrated by taking the example of climbing a step, a common problem for people considering a TJR. The impairments might include reduced joint movement, pain on movement and muscle weakness; the resulting activities limitations might be difficulty climbing stairs, and/or difficulty getting onto a bus. Consequent participation restrictions might be inability to get to the shops, or to go to stay with grandchildren because of the stairs at their home. Research has shown that the relationship between the I, A, and P domains of the ICF are not simple, with other factors such as self-efficacy and co-morbidities acting as independent determinants of the relationships between these variables [17].

**Figure 1 F1:**
[figure not shown]
International Classification of Functioning, Disability and Health.

Commonly used methods to assess function do not link up well with the ICF [15], but they too can be split into a number of different categories. In general we can use one of three different approaches:

1) Self-assessment, in which the person tells us what they can and cannot do, usually via a questionnaire.

2) Functional tests carried out in a clinic or laboratory, which may be observed or measured in an objective manner, such as timing or motion analysis.

3) Real-life observation or assessment, which can include covert monitoring of the sort used in insurance case assessment, or the utilisation of modern accelerometers which can monitor what activities are undertaken over a prolonged period of time. (This approach may well take over in the future, but it will not be considered further as we have not been able to investigate it)

There are many different techniques that can be used to assess function within each of these three general categories, and several of the most popular ones mix up both the different categories within the ICF classification, and the different assessment approaches. Therefore it is perhaps not surprising that a recent systematic review found extensive variation in the outcome measures used in clinical trials of TJR [18], and that other studies have found low-modest correlations between the different methods [19-22].

It has been recommended that a combination of outcome measures should be used to assess function after TJR [19,23]. However, there are many reasons not to use a wide number of measures with every patient, whether in clinical practice or research. These include patient fatigue and burden, time constraints of clinic and research appointments and time taken to process and analyse multiple information sources. Therefore, there is a need for guidance about which outcome measures are the most useful in assessing function before and after TJR. The aims of this study are to compare the properties and responsiveness (ability to identify responders and non-responders to TJR) of a selection of commonly used measures that are either self-assessment tools or functional tests, to examine how well they relate to the ICF concepts of I, A and P, and to explore the changes in the measures and domains of outcome over time.

## Methods

The ADAPT study (Assessing Disability After Partial and Total joint replacement) is a single-centre cohort study currently underway at the Avon Orthopaedic Centre (AOC). The AOC, based in the Southwest of England, is one of the largest elective orthopaedic units in the UK, with approximately 800 hip operations and 800 knee operations performed in 2011[24]. The ADAPT study has been approved by Southwest 4 Research Ethics Committee (09/H0102/72) and all participants provide their informed, written consent to take part. The study is registered on the NIHR Clinical Research Network Portfolio (UKCRN ID 8311).

### Study duration

Recruitment into the study began in February 2010 and finished in November 2011. The 1-year follow-up for all participants is anticipated to be complete by December 2012.

### Inclusion criteria

Patients listed for one of the following operations were eligible: primary total knee replacement, revision total knee replacement, unicompartmental knee replacement, patellofemoral replacement, primary total hip replacement, revision total hip replacement or hip resurfacing. Patients were recruited from a diversity of surgical procedures so that outcome measures could be assessed across their full range.

### Exclusion criteria

Patients were excluded from the study if they lacked the capacity to provide informed consent. This was assessed by the research nurse in accordance with guidance from the integrated research application system, which is responsible for providing ethical approval in the UK, and the Mental Capacity Act of 2005 [25]. This decision was made by a research nurse if the patient met one of the following criteria: 1.) they could not understand the information relevant to the decision to participate 2.) they were unable to retain the information about the study 3.) they were unable to use or weigh that information as part of the decision-making process 4.) they were unable to communicate their decision about participation (whether by talking, using sign language or any other means). Another exclusion criterion was severe functional limitations such that the participant was unable to walk as this would prevent the participant from being able to attempt any of the functional tests which would make it impossible to collect essential data. This was assessed in the discussion between the research nurse and the potential participant about what participation would involve and was always a mutual decision by the researcher and the patient. Being unable to complete questionnaires in the English language was also an exclusion criterion because not all the validated questionnaires have been translated into other languages.

### Participant recruitment

Potential participants were identified from the arthroplasty waiting list by the code for the intended operation and sent a postal invitation. Patients who returned a reply form were telephoned by a research nurse to discuss participation. This included a full explanation of study involvement, and a preliminary eligibility assessment by asking about the intended operation and assessing understanding of the information provided. Those that did not reply or who were missed from the initial postal invitation list due to late scheduling of hospital appointments were approached by a research nurse when they attended the pre-operative assessment clinic. These patients were identified by daily checking of the clinic lists. If they were interested, eligibility was assessed and a full explanation of study involvement was provided. The first appointment was arranged then or they were telephoned a few days later if they needed time to consider. In order to explore whether the patients enrolled in the study were representative of those undergoing TJR, all eligible participants were entered on a database on which data about age, gender and postcode were recorded.

### Assessment times

Participants attend a mutually convenient research appointment, lasting approximately one hour, at the AOC. Appointments are scheduled before surgery and then at 3-months and 1-year after surgery. Assessments are conducted at 3-months post-operative to coincide with the standard clinical review, by which time most patients have experienced a large improvement in pain and function [26]. Assessments are also conducted at 1-year post-operative as outcomes can continue to improve up until this time point [26]. The inclusion of two post-operative assessments also allows exploration of outcome trajectories and comparison of rates of improvement between different outcome domains (e.g. pain, function, participation).

At the initial pre-operative appointment eligibility was confirmed, informed written consent was obtained and a questionnaire was given to participants to return by post before their operation. For the post-operative assessments, a questionnaire is sent out prior to the research appointment. At each time point, participants undergo a clinical assessment. These assessments are conducted by trained research nurses who follow standard operating procedures to ensure consistency and standardisation in data collection and who were assessed for competency in the examination procedures by a senior research nurse and orthopaedic surgeon. Risk assessments of the functional tests were undertaken and safe operating procedures specified. The data collected during the assessments are recorded by the research nurses on standardised proformas.

### Selection of outcome measures

Table 1 provides a summary of the functional assessment measures used in this study. The Table also provides an overview of the ICF domains included within each functional assessment measure, with classification of self-completed PROMs and clinician-administered measures based on the results of an expert consensus study by Pollard and colleagues [15]. There are a number of other measures that could have also been included in this study such as the Oxford hip and knee scores [27,28], Hospital for Special Surgery Score [29], Knee injury and Osteoarthritis Outcome Score [30] and Nottingham Health Profile [31]. However, to avoid participation burden and fatigue only a selection of measures was chosen, which are outlined below.

**Table 1 T1:** Summary of measures used to assess function pre-operatively and at 3-months and 12-months post-operatively

	**ICF domains assessed**			**Mode of completion**	**Scoring**
	**I**	**A**	**P**		
**Patient-reported outcome measures***					
WOMAC function subscale		++	+/−	Patient	0-68
Ab-IAP	++	++	++	Patient	I scale = 9–45, A scale= 17–85, P scale = 9-45
SF-12 Physical Component Score	+/−	++	+/−	Patient	0-100
MYMOP2^†^	+/−	+/−	+/−	Patient with assistance from research nurse	0-6
**Clinician-administered measures**^**#**^					
American Knee Society Score	+	++	-	Research nurse and patient	0-100
Harris Hip Score	+	++	+/−	Research nurse and patient	0-100
**Performance tests and motion analysis**^**#**^					
Timed 20-metre walk	-	++	-	Research nurse and patient	Time, difficulty, motion parameters
Timed Get up and go test	-	++	-	Research nurse and patient	Time, difficulty, motion parameters
Sit to stand to sit	-	++	-	Research nurse and patient	Completion, difficulty, motion parameters
Step tests	-	++	-	Research nurse and patient	Completion, difficulty, motion parameters
Single stance balance tests	-	++	-	Research nurse and patient	Completion, difficulty, motion parameters

ICF= International Classification of Functioning, Disability and Health, I=Impairments, A=Activity limitations, P=Participation restrictions.

The extent to which I, A and P is assessed within each tool is indicated using the following symbol system: - no items assessing domain, −/+ a small number of items assessing domain, + some items assessing domain, ++ the majority of items assessing domain.

*Scores are self-completed by the patient in a postal questionnaire, excepting MYMOP2 which is completed during a research appointment.

^†^The MYMOP2 asks patients to generate two symptoms (impairments or activity limitations) and one activity (which could be activity limitation or participation restrictions) that is restricted by their symptoms.

^**#**^Scores and tests are assessed by a research nurse during a research appointment. The patients are also invited to rate their performance on the functional tests.

### Patient-reported outcome measures

The following validated measures are used to provide disease-specific and generic self-reported measures of outcome:

***Western Ontario and McMaster Universities Osteoarthritis index (WOMAC) function scale***[32]: This disease-specific subscale, validated in OA patients, consists of 17 questions assessing the extent of function limitations when performing a range of daily activities. Responses are provided on a 5-point Likert-type scale.

***Aberdeen Impairment, Activity Limitation and Participation Restriction Measure (Ab-IAP)***[33]: This 35-item disease-specific measure, validated in OA patients, uses the ICF framework to assess disability and produces scores for I, A and P. Responses are provided on a 5-point Likert-type scale.

***Short-form 12 (SF-12)***[34]: This 12-item general health measure produces a Physical Component score and Mental Component score scale. Responses are provided as binary options (yes/no) or on a Likert-type scale.

***Measure Yourself Medical Outcome Profile 2 (MYMOP2) ***[35]: This patient-generated instrument allows participants to generate and rate the severity of two symptoms that are concerning them and one activity important to them that is restricted by the symptoms. Participants also rate their general well-being, duration of symptom 1 and medication usage for symptom 1. At follow-up, participants are asked to rate the severity of the symptoms and degree of restriction of the activity that they identified at the first data collection point. Ratings are provided on scales of 0–6. The MYMOP2 is completed during research appointments by participants with the assistance of research nurses.

Participants also complete a number of other questionnaires to assess factors that have been found to influence outcomes after TJR (Table 2). At each assessment time, participants complete the Hospital Anxiety and Depression Scale [36] and the WOMAC Pain and Stiffness Subscales [32]. Participants are also asked to rate how disabled they perceive themselves because of their joint problems and why, and to list three things that they are hoping for from their TJR. Pre-operatively, medical co-morbidities are recorded using the Functional Co-morbidity Index [37] and information is collected about socioeconomic status (marital status, living arrangements, educational attainment, employment status), joints affected by arthritis, and previous surgery on other joints. In the 1-year post-operative questionnaire, satisfaction with the outcome of surgery is assessed using the Self-Administered Patient Satisfaction Scale for Primary Hip and Knee Arthroplasty [38].

**Table 2 T2:** Summary of measures used to assess factors influencing function

	**Dimensions**	**Mode of completion**	**Scoring**	**Assessment times**		
				**Pre-op**	**3-month**	**1-year**
WOMAC pain subscale	Joint pain	Patient	0-20	✓	✓	✓
WOMAC stiffness subscale	Joint stiffness	Patient	0-8	✓	✓	✓
Hospital and Anxiety Depression Scale	Depression, anxiety	Patient	0-21	✓	✓	✓
SF-12 Mental Component Score	Mental health	Patient	0-100	✓	✓	✓
Perceived level of disability	Function	Patient	0-10	✓	✓	✓
3 things hoping for from surgery	Expectations	Patient	Categorical	✓	✓	✓
Functional Co-morbidities Index	Co-morbidities	Patient	0-18	✓		
Arthritis and surgery in other joints	Co-morbidities	Patient	By joint/count	✓		
Socioeconomic status	Socioeconomic	Patient	Categorical	✓		
Self-Administered Patient Satisfaction Scale	Satisfaction	Patient	0-100			✓

### Clinician-administered measures

The Harris Hip Score is completed with hip replacement patients and the American Knee Society Score is completed with knee replacement patients.

***Harris Hip Score (HHS) ***[9]**:** This assessment measure provides a total score of between 0–100 (worst to best) collected over 4 domains. Function, which includes limp, use of assistive devices, walking distance, managing stairs, using public transport, sitting comfortably and putting on shoes and socks, is weighted the most heavily and is assigned 47 points. Pain is assigned 44 points. The physical examination involves assessing deformity (4 points) and range of motion (5 points).

***American Knee Society Score (AKSS)***[10]: This assessment consists of a Knee Score and a Function Score, both with a total score ranging from 0–100 (worst to best). The Knee Score incorporates examiner’s rating of patients’ pain (50 points) and a clinical assessment of stability (25 points) and range of motion (25 points), with deductions for flexion contracture, extension lag and misalignment. The Function Score consists of questions about walking distance (50 points) and stair climbing ability (50 points), with deductions for the use of walking aids.

### Performance tests

Before performing each of these tasks, participants are asked if they think they will be able to perform the task and estimate how difficult they think the test will be to perform on a 0–10 scale (no difficulty at all to impossible). After they have completed the test, they are then asked to rate how difficult the task actually was to perform on the same 0–10 scale. The research nurse conducting the assessment also provides a rating of how difficult it appeared to be for the participant to perform the task. If participants are unwilling to attempt the test or the research nurse is unhappy to proceed because of safety concerns, the test is not performed. All tests are performed without the use of supportive aids except the timed 20 metre walk and are described in the order in which they are performed.

***Timed 20-metre walk***[39]: Participants are timed as they walk a 20-metre straight distance on level ground at their normal, comfortable speed. If the participant normally uses a walking aid they are asked to try without it but if they feel unable to do so, they complete the test using the walking aid. The recorded outcome is the time taken to complete the test.

***Timed get up and go test***[40]: Participants sit on a height adjustable chair such that a 90° angle is formed when the femur is horizontal and the tibia vertical with their feet shoulder width apart and their arms crossed against their chest. Participants are timed as they stand up from the chair without using their hands, walk at a normal pace past a marker three metres away, turn around, walk back and sit down again. The recorded outcome is whether participants are able to complete the activity and how long it took.

***Sit-to-stand-to-sit***[41]**:** Participants sit on a height adjustable chair as described for the previous test. Participants then stand up, wait two seconds and sit down again without using their hands. The recorded outcome is whether participants are able to complete the activity.

***Step test***[42]: Participants step up onto a 20cm high block leading with the contra-lateral leg, wait two seconds, and then step down from the block with the index leg leading, without using their arms. The test is then repeated with the index leg leading. If participants successfully completed this test, the test is repeated with a 30cm block. The recorded outcome is whether participants are able to complete the activity.

***Single stance balance test***[43]: Participants stand with their feet together facing the research nurse and place their palms gently on top of the research nurses’ palms. Participants then lift their index leg and attempt to balance on their contra-lateral leg for 15 seconds. If the participant loses balance within three seconds, then the test is reattempted. If the participant loses balance before 15 seconds, the length of time is recorded. This test is then repeated while balancing on the index leg. If these tests are completed successfully, the participant repeats the tests with no stability support from the research nurse. The recorded outcome is whether participants are able to maintain the stance for 15 seconds.

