### Inertial sensor based motion and gait analyses

Movement analysis by body-fixed inertial sensors containing accelerometers and gyroscopes enables the objective assessment of the translational and angular movements of body segments outside a gait laboratory [44,45]. We used a single 3D inertial sensor (41x63x24mm; 39g; Microstrain Inertia Link) containing accelerometers (±5g) and gyroscopes (±300°/s) along the three orthogonal axes in frontal, sagittal and transverse plane and positioned centrally between both posterior superior iliac spines to measure trunk movements near the center of gravity. Based on the 3D linear accelerations, angular rates and angular positions put out by the sensor and send wirelessly to a PC at a 100Hz sampling frequency via a Bluetooth link, analysis algorithms calculate motion parameters such as step frequency, step asymmetry or trunk sway.

The inertial sensor was used to derive motion parameters from a battery of movement tasks which are clinically feasible to perform during a routine outpatient visit and which challenge the patient’s functional capacity in different ways: 1) locomotion (walking); 2) transfers (sit-stand-sit, get up and go); 3) rising and descending (step test) and 4) balance tests (single leg stance). The walk test [46] and the step-test are repeated twice and the sit-stand-sit test is repeated three times to derive representative mean values or study possible effects of fatigue or warming up.

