#### Inertial sensor analysis

Real-time data from the inertial sensor will be stored on a computer with a sampling frequency of 100Hz. After manually selecting the start and end of each test, self developed algorithms based on previously published principles [60] will automatically derive a motion parameter set for each test e.g. for gait, spatiotemporal parameters will be derived after heel strike detection based on the zero crossing method described by González and colleagues [61] and pelvic angles will be derived by common peak detection methods. Automated peak detection after signal filtering is also the main principle to derive the motion parameters for the step, get up and go, sit-stand-sit and the balance tests. In addition, measuring the time to task achievement for each test is more accurate and reproducible from the sensor signal than from a stop watch. For tests with repetitions (e.g. sit-stand-sit) the average values will be reported. All signal analysis and motion parameter calculations will be programmed in MATLAB® (MathWorks®) version R2009a.

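### The single stance balance test records hold time in seconds, but its named outcome is only pass or fail at 15 seconds, which can cost a substantial part of its sensitivity to change

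*Protocol article*

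**What the plan says.** The article's description of the single stance balance test (under Performance tests) asks the participant to "attempt to balance on their contra-lateral leg for 15 seconds", then repeats the test on the index leg. On partial performance it says: "If the participant loses balance before 15 seconds, the length of time is recorded". A harder stage follows: "If these tests are completed successfully, the participant repeats the tests with no stability support from the research nurse". The paragraph closes by fixing the outcome: "The recorded outcome is whether participants are able to maintain the stance for 15 seconds".

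Table 1 agrees with that last sentence. The scoring entry for the balance tests is "Completion, difficulty, motion parameters". The rows for the 20-metre walk and the get up and go test list time as well.

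Three other statements bear on the point:

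- Patients "rate how difficult the task actually was to perform on the same 0–10 scale" after each performance test, and the nurse gives a separate rating.
- Single leg stance is one of the sensor tasks, and "analysis algorithms calculate motion parameters such as step frequency, step asymmetry or trunk sway".
- The Inertial sensor analysis section says that "measuring the time to task achievement for each test is more accurate and reproducible from the sensor signal" than from a stop watch.

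Under Quantitative analysis, internal responsiveness is planned for self-reported and clinician-administered tools. Performance test outcomes are related to responsiveness through generalized linear models. Change in the measures across the three visits is studied with mixed or marginal models, and raw scores may be transformed or categorised after their distributions have been inspected.

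**The concern.** A graded measurement is taken and then left out of the named outcome. Among the five performance tests this happens only here. The walk is scored by its time, and get up and go by completion and time. For sit-to-stand-to-sit and the step test no nurse-recorded time is described. The balance test alone has a recorded time that its outcome ignores.

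The study exists to compare the properties of functional measures and their change over time. A yes/no balance result will stand beside continuous walk times and 0–68 or 0–100 scores. Every improvement that stays below 15 seconds is scored as no change, so a weak association or a flat trajectory could reflect the coding and not the test. An MCID is planned for each measure. If that is meant to include the performance tests, a yes/no outcome offers no scale on which to place one.

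**Working it through.** The document gives no power, effect size, pass rate or distribution of hold times, so there is no stated figure to reproduce. What follows sizes the loss under assumptions.

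**From the document:** seconds recorded on failure; ceiling 15 s; 2 legs × 2 support stages = up to 4 results; 133 + 130 = 263 patients; significance level 0.05 (taken as two-sided).

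**Assumed:** log-normal latent hold time with log-SD 0.6, 1.0 or 1.4; pre/post correlation 0.3 or 0.6; improvement of 0.2 SD on the log scale; baseline pass rate 10% to 90%.

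**Step 1: textbook bound, no ceiling.** Cutting a normal score at c, with a proportion p above it, keeps φ(c)² / [p(1 − p)] of the information.

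- p = 0.5: 0.3989² / 0.25 = 0.64
- p = 0.2 (or 0.8): 0.2800² / 0.16 = 0.49
- p = 0.1 (or 0.9): 0.1755² / 0.09 = 0.34

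This bound is too pessimistic at high pass rates. The recorded time stops at 15 s, so seconds say nothing more about those who pass.

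**Step 2: with the 15 s ceiling.** For 2,000,000 simulated pre/post pairs per setting, relative efficiency = (mean change / SD of change)² for pass/fail, divided by the same quantity for capped seconds. Example with log-SD 1.0, correlation 0.6 and a baseline pass rate of 50%: pass/fail 0.0791 / 0.5421 = 0.146; seconds 0.740 / 4.259 = 0.174; (0.146 / 0.174)² ≈ 0.70. Ranges over all six combinations of log-SD and correlation:

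| Baseline pass rate | Efficiency kept by pass/fail | Loss |
|---|---|---|
| 10% | 0.25–0.41 | 59–75% |
| 20% | 0.39–0.54 | 46–61% |
| 30% | 0.52–0.64 | 36–48% |
| 50% | 0.70–0.81 | 19–30% |
| 70% | 0.87–0.99 | 1–13% |
| 80% | 0.94–1.09 | none to 6% |
| 90% | 1.06–1.20 | none |

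At n = 263, log-SD 1.0 and correlation 0.6, power for pass/fail versus seconds is 0.40 vs 0.89 (10% pass), 0.66 vs 0.81 (50%) and 0.49 vs 0.50 (80%).

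**Step 3: check with actual tests.** A separate simulation used 130 pairs, correlation 0.6 and 2,000 runs, comparing exact McNemar on pass/fail with Wilcoxon on capped time. Power is converted to efficiency as [(1.96 + z of power, pass/fail) / (1.96 + z of power, time)]².

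| Shift | Pass rate | Power, pass/fail vs time | Efficiency kept |
|---|---|---|---|
| 0.3 SD | 30% | 0.602 vs 0.907 | (2.219 / 3.283)² = 0.46 |
| 0.3 SD | 50% | 0.639 vs 0.812 | (2.316 / 2.845)² = 0.66 |
| 0.3 SD | 70% | 0.510 vs 0.619 | (1.985 / 2.263)² = 0.77 |
| 0.2 SD | 30% | 0.286 vs 0.581 | (1.395 / 2.164)² = 0.42 |
| 0.2 SD | 50% | 0.309 vs 0.486 | (1.461 / 1.925)² = 0.58 |
| 0.2 SD | 70% | 0.262 vs 0.351 | (1.323 / 1.577)² = 0.70 |

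These losses are somewhat larger than in Step 2, partly because exact McNemar is conservative. The pattern is the same: the fewer patients who pass at baseline, the more pass/fail costs.

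**The case against.** The strongest reply is that pass/fail is one component of a richer measure. Two difficulty ratings, sensor parameters such as trunk sway, and the progression from supported to unsupported stance on each leg are all kept. The seconds are collected, so nothing is irrecoverable. The analysis section says that it is not a full account and allows raw scores to be rescaled. Internal responsiveness is not planned for performance tests at all. The study is exploratory without a sample size calculation, and the shifts, correlations and pass rates used above are invented.

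Much of this stands, and it rules out three readings that a reader might infer. The balance test is not reduced to a bare yes/no, because Table 1 keeps difficulty and motion parameters. The document does not set out an internal responsiveness analysis in which this test would be judged unresponsive. And the data are not lost.

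It does not remove the point. Difficulty and sway are different quantities from hold time. Permission to transform raw scores does not commit anyone to analysing the seconds when the named outcome and Table 1 both leave them out. The sensor section's reference to timing each test makes the missing time in Table 1 less coherent, not more. The outcome is stated outright in two places, so this is a choice made in the document and not a detail left to an analysis plan. Performance tests still enter the association models and, as measures, the change-over-time models.

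**Conclusion.** The point holds as a moderate weakness. The protocol article names a pass/fail outcome where a capped time is already collected, and this can cost a substantial part of the test's sensitivity in the association and longitudinal analyses. A reader might go further and say that most of the sensitivity is thrown away. The document does not support that, because it gives no pass rate. Under the assumptions above, more than half is lost only if about 20% or fewer hold 15 s at baseline (up to about 30% in the test-based check). The loss is roughly 20–35% if half do, reaching 42% in the test-based check with the smaller shift, and near nil at 80% or more when means are compared. The figures treat one stance at a time and ignore the re-attempt after an early loss of balance.

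**What to change.** Name hold time (0 to 15 s, right-censored at 15 s) as an outcome for each leg and support stage, and add time to the balance row of Table 1. Analyse it by ranks or with a censored or ordinal model, and keep pass/fail at 15 s as a descriptive summary.

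No extra data collection is needed. The cost is some added analysis work and three short rules, which should be written before the data are examined:

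- which time counts when the test is re-attempted after balance is lost within three seconds;
- how an unsupported stage is scored when it was not reached;
- how a test that was not attempted, through unwillingness or safety concerns, is scored.
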